#### Motivational interviewing

In the FGD’s employees had reported that they enjoy the wellness and screening days offered by their health insurer and employer, and that they value the expertise of the healthcare professionals conducting the testing. Thus, the wellness counsellors, all of whom have had previous paramedical training (e.g. physiotherapist, exercise physiologist, dietician) will receive Motivational Interviewing training, in the form of a 3-day workshop, followed by 3 months of active training, from an accredited tertiary institution. The decision to give the wellness specialists three months of active training was based on the need to establish competency in motivational interviewing prior to initiating the intervention.

The intervention will consist six counselling sessions, whereby the first and last sessions will be face to face while the remaining four sessions will be telephonic. Employees in the FGD preferred face-to-face interactions, but due to time and logistical constraints, telephonic consultations will be included. Furthermore, one-on-one counselling sessions incorporating motivational interviewing principles, and which include telephonic sessions have been shown to be effective [19]. The aim of the first face-to-face session is to establish goals and strategies to improve health behaviour. The following four sessions will allow the counsellor to monitor progress towards the goal, set new goals or to adjust strategies to achieve a previously determined goal. The final session will comprise of a re-assessment of health and clinical outcomes, and for the employee to set additional goals or to discuss strategies to maintain healthy behaviours achieved.

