### Step 5: Adoption and implementation plan

#### Pilot study

A pilot study was conducted in a convenient sample of employees for 12 weeks. The aim of the pilot was to determine the feasibility of the interventions and also to allow the counsellors to gain experience and proficiency in motivational interviewing techniques.

Eight wellness counsellors, based in three different South cities, recruited a convenience sample of both male and female employees (n = 225). The baseline participant characteristics are presented in Table 2. Despite the mean serum cholesterol and blood pressure being within normal ranges, more that 80% of the employees volunteering to participate had two or more risk factors for cardiovascular disease.

**Table 2 T2:** Baseline characteristics of participants in the pilot study

	**n**	**Mean**	**± Standard Deviation**
Age (years)	225	40.0	10.8
Men (% of total sample)	121	51%	
Body Mass Index (kg/ht2)	225	31.0	5.5
Cholesterol (mmol/l)	228	4.7	0.9
Diastolic Blood Pressure (mm Hg)	229	84.1	11.6
Physical Activity (min/wk)	225	63.0	120.9

The analysis of covariance (ANCOVA) was performed to measure the effectiveness of the 12-week intervention. Participants were grouped into being either at risk or not at risk for each of the individual risk factors, and then the baseline and follow up measures were compared for each specific risk factor. Diastolic blood pressure decreased significantly over the 12 weeks period among those whose baseline result placed them in the at risk group (Diastolic blood pressure more than 90 mmHg) from 95.8 mmHg ± 9.8 to 90.1 mmHg ± 13.7 (p < 0.0001). Similarly, those with 2 or more risk factors at baseline decreased their number of risk factors from 3.5 ±0.8 to 3.0 ± 1.0 at follow up (p < 0.0001). In addition, there was a significant group and time effect for Body Mass Index, where those who were overweight or obese (BMI >25) at baseline experiencing a slight decline at 12 weeks (data not shown). This is an encouraging finding as 83% of the participants were either overweight or obese at baseline.

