#### Sample size calculation

The sample size was determined according to a power calculation using a dichotomous variable: meeting the PA guideline with at baseline 50% not meeting the guideline and after the intervention 40% (intervention group) vs 50% (in control group). Based on these numbers, and 80% power and significance of 0.05, 775 employees are required at the 12-month follow-up with 387 in control group and 387 in intervention group. Thus, assuming that approximately 20% of participants will be lost to follow-up at 12 months, we will aim to recruit 928 employees at baseline and allocate 424 to the intervention and control groups (Figure 1).

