### Statistical analyses

STATISTICA software package will be used for all the analyses (Stasoft, Inc. 184–199, Tulsa OK, SA) and intention to treat analysis will be performed for each of the outcomes. Mean, standard deviation and standard error will be calculated for the continuous variables. Frequency tables will be used to determine the percentage of individuals at risk. An Analysis of Variance (ANOVA) will be performed to determine whether there were significant changes in physical activity habits and nutrition in the intervention and control groups at 6 and 12 months.

The cost-effectiveness of the intervention programme will be determined from the societal and the employer perspective. Confidence intervals around differences in costs between the intervention groups and control group will be estimated using bootstrapping techniques. Cost effectiveness ratios will be calculated by dividing the difference between the mean total costs of the intervention groups and control group, by the difference in the mean habitual physical activity levels and total number of risk factors for cardiovascular disease. Uncertainty around the cost-effectiveness ratios will be graphically presented on Cost-Effectiveness planes (CE-planes) [34]. Furthermore, Cost-effectiveness acceptability curves will be estimated to show the probability of cost-effectiveness at different ceiling ratios [35].

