## Discussion

We have identified a need for worksite health promotion programs in South Africa to address the increasing prevalence of CVD and the associated risk factors, which is the underlying rationale for the Working on Wellness - WOW - worksite intervention research study. This intervention aims to identify employees at increased risk for cardiovascular disease and provide them with counselling, through motivational interviewing, to equip them to reduce their risk factor profiles.

This approach is supported by previous research which showed that face to face counselling in the worksite resulted in increased physical activity, improved cardiovascular fitness, decreased body fat percentage and serum cholesterol concentrations [22]. In addition, both employers and employees participating in the formative assessment expressed a desire for interventions which address CVD and the associated risk factors. Furthermore, the preliminary results from the pilot study supports the high risk approach based on the trends in reduction in risk after only 12 weeks of intervention. Despite the promising results of the pilot study, the limitations of not having a control group needs to be acknowledged.

The adherence to the Motivational Interview techniques will be monitored during the course of the intervention where at least 12 audio-recordings per wellness specialist will be coded using the MITI scoring. Thus, this research study will also be able to provide more insight into the fidelity of the intervention.

Worksites have been identified as opportune settings for health promotion and intervention programs. However, there is still no conclusive evidence on the effectiveness of these programs on employee health, as reviews have shown that results are still ‘somewhat equivocal’ [36]. A need for further research in the worksite has been identified which includes randomised control trials in order to provide more evidence on the effectiveness of intervention programs [37]. This research study aims to contribute to the current knowledge and provide new insight into the ffectiveness of worksite intervention programs targeting employees at increased risk for cardiovascular disease. The economic evaluation of the intervention may also provide new knowledge on the cost effectiveness of one-on-one counselling for employees.

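### The planned ANOVA allows for neither company nor counsellor clustering; modelling company alone may leave the standard error too small if specialists serve several companies

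*Protocol article*

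**What the plan says.** - **Randomisation.** The Randomisation section of the protocol article allocates whole companies to intervention or control.
- **Delivery.** The Intervention group section offers individual counselling sessions to intervention employees. The Control group section gives usual care with no counselling sessions. The Motivational interviewing section describes the staff as "the wellness counsellors, all of whom have had previous paramedical training (e.g. physiotherapist, exercise physiologist, dietician").
- **Number of specialists.** The only figure is for the pilot: "Eight wellness counsellors, based in three different South cities, recruited a convenience sample". The article does not give the number of specialists in the main trial, their allocation to companies or the number of companies.
- **Fidelity.** The Discussion says that "at least 12 audio-recordings per wellness specialist will be coded using the MITI scoring". Process measures presents this scoring as a check on fidelity and adherence. It does not enter the outcome analysis.
- **Analysis.** Statistical analyses states: "An Analysis of Variance (ANOVA) will be performed to determine whether there were significant changes in physical activity habits and nutrition". The Abstract names the same method. Neither place mentions company or specialist.
- **Sample size.** The effect is "at baseline 50% not meeting the guideline and after the intervention 40% (intervention group) vs 50% (in control group"), and with "80% power and significance of 0.05, 775 employees are required at the 12-month follow-up", split as "387 in control group and 387 in intervention group". No design effect appears.

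**The concern.** An ANOVA on employees takes each employee as an independent observation. The design gives two reasons to doubt that. Employees of one company share a workplace and were allocated together. Intervention employees who see the same specialist may also share that specialist's skill and style. The second source exists in the intervention groups only, because controls have no counselling sessions; this is a partially nested design.

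If either correlation is positive, the confidence interval for the programme effect is too narrow and a null effect is declared significant more than 5% of the time. A result that depends on a few able counsellors could then be read as a result of the programme in general. The two sources need separate thought, because a company term covers the specialist source only under some staffing arrangements.

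**Working it through.** **1. The plan's own figure.** For 50% against 40%, two-sided 0.05 and 80% power:

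n per arm = [1.960·√(2·0.45·0.55) + 0.842·√(0.25 + 0.24)]² / 0.10² = (1.379 + 0.589)² / 0.01 = 387.3

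Twice this is 774.7, which is the stated 775. Power at 387 per arm is 79.97%. The stated size therefore reproduces with independent employees and no allowance for clustering.

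**2. Assumptions.** The article gives no ICC, so these are ranges.
- 8 specialists, as in the pilot; 6 to 16 for sensitivity.
- Counsellor ICC 0.01, 0.02 and 0.05.
- Company ICC 0.02.
- The 3-month and 6-month groups are pooled as one arm of 387, as in the sample size section.

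**3. Plain ANOVA, counsellor correlation only.** Employees per specialist: 387/8 = 48.4. The design effect in the intervention arm is DE = 1 + 47.4·ICC, and in the control arm it is 1. The standard error (SE) ratio for the difference is √[(DE + 1)/2], and the true error is 2·[1 − Φ(1.96/ratio)].

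| Counsellor ICC | DE | SE ratio | True error of a nominal 5% test |
|---|---|---|---|
| 0.01 | 1.47 | 1.11 | 7.8% |
| 0.02 | 1.95 | 1.21 | 10.6% |
| 0.05 | 3.37 | 1.48 | 18.5% |

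Using the planned binomial variances (0.25 and 0.24) instead of equal ones gives ratios of 1.11, 1.21 and 1.47 and errors of 7.7%, 10.5% and 18.2%. With those variances and a correct standard error, power at 387 per arm is 72%, 64% and 48%. Over 6 to 16 specialists the SE ratio runs from 1.06 to 1.60.

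**4. Plain ANOVA, company correlation only.** At company ICC 0.02 with no counsellor effect, simulated error (20,000 runs per setting) is 25%, 16%, 11% and 9% with 4, 8, 16 and 24 companies per arm.

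**5. Company-level test, with a counsellor effect present.** Let there be K companies per arm, q = K/8 companies per specialist and m = 387/K employees per company. On a unit-variance scale with company ICC c and counsellor ICC t:

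- variance of an intervention company mean: V = c + t + (1 − c − t)/m
- average covariance between two intervention companies: C = t(q − 1)/(K − 1)
- intervention-arm variance as estimated: (V − C)/K; true value: V/K + C(K − 1)/K
- control-arm variance: [c + (1 − c)/m]/K

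Example with K = 16, q = 2, c = t = 0.02: m = 24.2, V = 0.0797 and C = 0.00133. The estimated intervention variance is 0.00490, the true one 0.00623 and the control one 0.00378. SE ratio = √[(0.00623 + 0.00378)/(0.00490 + 0.00378)] = 1.07.

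With q = 1, C = 0 and the ratio is exactly 1.00. Simulated error of the company-level t-test (20,000 runs; Monte Carlo standard error about 0.15 to 0.2 percentage points):

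| Companies per specialist | Counsellor ICC 0.01 | 0.02 | 0.05 |
|---|---|---|---|
| 1 (K = 8) | 5.2% | 5.2% | 5.1% |
| 2 (K = 16) | 6.0% | 6.8% | 9.0% |
| 3 (K = 24) | 6.5% | 7.8% | 11.0% |

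The analytic SE ratios for two or three companies per specialist run from 1.04 to 1.23.

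**The case against.** **A company-level analysis may be enough.** If each specialist works in one company, counsellor variation lies inside the randomised unit and a correct company-level analysis already includes it. This stands. A reader might infer that the standard error stays too small whenever only company is modelled. The documents do not support that, and step 5 shows no excess error in the one-company case.

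**Shared specialists are not documented.** A reader might also infer from the pilot's eight counsellors in three cities that specialists in the main trial cover several companies. That sentence describes the pilot only. The damaging cases above also need 16 or 24 companies per arm, which the article does not state. The objection stands in that this part must remain conditional, but the article does not exclude it either.

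**A counsellor effect is not shown.** Mixed professions and per-specialist fidelity scoring make a non-zero effect plausible but do not demonstrate one. The three months of active training is meant to reduce such differences. This stands, and it is why the ICC is given as an assumed range.

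**Ignoring company is the firmer defect.** This stands as well. Step 4 involves no counsellor effect. The separate counsellor contribution is only what is left after company is modelled.

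**Model detail belongs in the analysis plan.** This is fair for the specialist random effect and its degrees of freedom. It does not dispose of the point, because the article is not silent: it names a test, in two places, for a design that the test does not fit.

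**Conclusion.** The point holds in conditional form. Followed as written, the ANOVA gives too small a standard error under any positive correlation within company or within specialist. At 8 specialists and a counsellor ICC of 0.01 to 0.05, the counsellor part alone gives a true error of about 8% to 18%.

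Once company is modelled properly, the remaining counsellor error is nil if each specialist serves one company. It is about 6% to 11% if each of 8 specialists serves two or three companies at a company ICC of 0.02. Apart from the 387 per arm, all inputs to these sizes are assumptions. The part separate from company clustering is therefore modest and uncertain, but it is cheap to guard against and should be addressed.

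**What to change.** In Statistical analyses, and in the Abstract to match:

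1. Replace the plain ANOVA with a model that has a company random effect and small-sample degrees of freedom.
2. State the number of specialists and how they are allocated to companies, and record the delivering specialist for every intervention employee.
3. If specialists serve more than one company, add a specialist random effect that applies in the intervention groups only, with degrees of freedom that reflect the numbers of specialists and companies. Make this at least a prespecified sensitivity analysis.
4. If each specialist serves one company, allow the company variance to differ by arm. With equal numbers of companies the equal-variance test already held its level in step 5, so this mainly protects against unequal numbers.

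The cost is one identifier, which the session bookings should already hold because specialists make the bookings, and a few lines of text. The downside is a somewhat wider interval.

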### Step 5: Adoption and implementation plan

#### Pilot study

A pilot study was conducted in a convenient sample of employees for 12 weeks. The aim of the pilot was to determine the feasibility of the interventions and also to allow the counsellors to gain experience and proficiency in motivational interviewing techniques.

Eight wellness counsellors, based in three different South cities, recruited a convenience sample of both male and female employees (n = 225). The baseline participant characteristics are presented in Table 2. Despite the mean serum cholesterol and blood pressure being within normal ranges, more that 80% of the employees volunteering to participate had two or more risk factors for cardiovascular disease.

**Table 2 T2:** Baseline characteristics of participants in the pilot study

	**n**	**Mean**	**± Standard Deviation**
Age (years)	225	40.0	10.8
Men (% of total sample)	121	51%	
Body Mass Index (kg/ht2)	225	31.0	5.5
Cholesterol (mmol/l)	228	4.7	0.9
Diastolic Blood Pressure (mm Hg)	229	84.1	11.6
Physical Activity (min/wk)	225	63.0	120.9

The analysis of covariance (ANCOVA) was performed to measure the effectiveness of the 12-week intervention. Participants were grouped into being either at risk or not at risk for each of the individual risk factors, and then the baseline and follow up measures were compared for each specific risk factor. Diastolic blood pressure decreased significantly over the 12 weeks period among those whose baseline result placed them in the at risk group (Diastolic blood pressure more than 90 mmHg) from 95.8 mmHg ± 9.8 to 90.1 mmHg ± 13.7 (p < 0.0001). Similarly, those with 2 or more risk factors at baseline decreased their number of risk factors from 3.5 ±0.8 to 3.0 ± 1.0 at follow up (p < 0.0001). In addition, there was a significant group and time effect for Body Mass Index, where those who were overweight or obese (BMI >25) at baseline experiencing a slight decline at 12 weeks (data not shown). This is an encouraging finding as 83% of the participants were either overweight or obese at baseline.

The intervention was well received by employees participating in the pilot study. They were encouraged that their health results obtained at their company’s wellness days could be improved upon. Most employees chose to increase levels of physical activity and improve various aspects of their diet such as increasing fruit and vegetable intake and decreasing daily fat consumption. Thus the improvements in clinical measures, and also the positive feedback from employees, supported the planned intervention.

### Step 6: Evaluation plan

#### Study design

The intervention as developed in the previous steps will be evaluated in a cluster-randomised controlled trial in South African worksites with a 12-month follow-up. The two intervention groups will receive 6 counselling sessions over either a 3 or 6-month period, described in Table 3. The control group will receive usual care. These participants will be unaware of the other two groups participating in the research study.

**Table 3 T3:** Timeline and contact schedule for employees in the intervention groups

**Week**	**6-month intervention group**	**3 month intervention group**
0	Wellness day at company. (Baseline measurement)	Wellness day at company. (Baseline measurement)
1	Face-to-face contact	Face-to-face contact
	(set goals, action plan)	(set goals, action plan)
4	Telephone contact	Telephone contact
	(monitor progress)	(monitor progress)
8	Telephone contact	Telephone contact
	(monitor progress)	(monitor progress)
12	Telephone contact	Face to face (final contact)
	(monitor progress)	
16	Telephone contact (monitor progress)	
20	Telephone contact	
	(monitor progress)	
24	Face to face (final contact)	
	(set new goal, plan way forward)	
26	First follow up measurement	
52	Second follow up measurement	First follow up measurement Second follow up measurement

#### Setting

The study will be conducted in cooperation with a major national private health insurer, Discovery Health. Large companies (>300 employees) that are clients of this insurer, offering health and wellness days and that are based in three South African cities will be eligible to participate in this study.

#### Study population

Over the course of two months, all employees from the eligible companies will be invited to participate in the wellness day(s) of their company. The health insurer will offer and conduct a Health Risk Assessment of risk factors, including: family history, Body Mass Index (BMI) and body fatness, blood pressure and finger-prick cholesterol and glucose concentrations, self-report physical activity and dietary intake behaviour, smoking, and stress, to the employees at the wellness day.

Those employees who are identified to be at ‘increased’ or ‘high’ risk for CVD, based on an adapted Framingham score of 10% or more [18] will be invited by the wellness specialists (via telephone call) to take part in the research study. Employees agreeing to participate will be asked to sign an informed consent and to provide their email address and contact details.

Because all the companies hosting wellness days in this research study are clients of a major national health insurer, it will be able to access data for employees who do not volunteer for the screening activities, and thus be able to compare responders to non-responders. Recorded data for all employees include healthcare expenditure and whether they participated in a health screening activity recently. The data for the employees who choose not to participate will be sent to the researchers without any personal identifiers, thus ensuring employee confidentially. Being able to describe the non-responders is one of the strengths of this study design, and the insured population with whom we are working, providing insight into the problem of selection bias.

#### Randomisation

Randomisation will take place at the company level, where participating companies will be assigned to either the intervention or the control group. The wellness specialists’ manager will assign each company with a number and then use a random numbers table to allocate the companies to either the intervention or control.

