### Step 4: Design of the intervention

Based on the first three steps of intervention mapping, it was determined that the intervention would be focused on employees at increased risk for cardiovascular disease, and that the program would be implemented by way of invitation for one-on-one counselling sessions with a wellness specialist.

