#### Blinding

Due to the nature of the research, the wellness specialists will not blinded and knew which companies were receiving the intervention. However, the employees participating in the research study were not aware of the expected outcomes of the study, nor were they aware of the other (either control or intervention) group participating in the research study.

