#### Inclusion and exclusion criteria for companies

Companies with 300 or more employees will only be selected from those willing to allow a repeat of the HRA onsite at 6 and 12 months follow-up. In addition, the employer should have employee absenteeism data from their employee records available.

One of the challenges with worksite health promotion programs is that the company management should “buy in” to the intervention and support its implementation, and also “buy in” to the study and be willing to being placed in the wait-list control arm of the study. These issues will be discussed with the company during recruitment. To emphasize the importance of continued support, we require a letter of commitment from the management of prospective companies for the duration of the study. Furthermore, the researchers will invite participation and seek approval from the respective unions and health and safety committees functioning at the companies.

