### Intervention group

The wellness specialists will calculate the adapted Framingham score for all employees who have voluntarily participated in their worksite’s wellness day. All employees who are identified as being at increased risk will receive a telephone call from the wellness specialist inviting them to participate in the research study. Should they agree, the wellness specialist will book the first face-to-face session, which will take place at the employee’s worksite.

Individuals in the intervention group will receive the same advice and health promotion materials as those in the control group. Additionally, they will be offered an individually tailored intervention that consists of one-on-one counselling sessions. The first intervention group will receive the six one-on-one counselling sessions over a 6-month period (6-I), while the second intervention group will receive the counselling over a 3-month period (3-I).

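### The counselling team's own manager numbers the companies and draws their allocation, so the randomisation is not independent of recruitment and delivery

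*Protocol article*

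**What the plan says.** All places are in the protocol article.

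- **Unit.** The Randomisation section fixes the company as the unit: "Randomisation will take place at the company level, where participating companies will be assigned to either the intervention or the control group".
- **Allocator and method.** The same section gives the draw to the person who supervises the wellness specialists: this "manager will assign each company with a number and then use a random numbers table to allocate the companies", which places each one in an arm.
- **Delivery.** Under Step 4, "the program would be implemented by way of invitation for one-on-one counselling sessions with a wellness specialist".
- **Recruitment.** Under Intervention group, "All employees who are identified as being at increased risk will receive a telephone call from the wellness specialist inviting them to participate". The Study population section also gives the telephone invitation to the wellness specialists.
- **Masking.** The Blinding section says that "the wellness specialists will not blinded and knew which companies were receiving the intervention". It does not mention the manager.
- **Company commitment.** The inclusion and exclusion criteria for companies name management support as a challenge, require a letter of commitment, and ask that management "be willing to being placed in the wait-list control arm of the study". These matters are raised with each company when it is recruited.

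**The concern.** A random draw protects a trial best when the person making it has no part in what follows and cannot tell which unit each number stands for. Here the draw is given to the line manager of those who will recruit and counsel, and that manager also attaches the numbers to known companies. Nobody else is given a role in the procedure, so if the draw were later questioned, the article points to no second person who could confirm that it was made once and as planned.

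What is at stake is comparability of companies between arms. Every participant's arm follows from the company's arm. Management support can differ from company to company, and it can be visible before the draw because it is discussed at recruitment. The primary outcome is a change in habitual physical activity, measured by a self-administered questionnaire, which a more supportive workplace could plausibly affect. An imbalance in support between arms could then be mistaken for an effect of counselling.

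**Working it through.** No arithmetic applies. The article gives no figure on this point and does not state the number of companies, so the check is a reading of the sections against each other.

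1. **Who controls the draw?** The Randomisation section gives numbering, table reading and assignment to one role. This is a stated choice, not a detail left out of a condensed article.

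2. **Is that role separate from recruitment and delivery?** No. It is defined as the manager of the wellness specialists. Step 4 has the specialists deliver the sessions; Study population and Intervention group have them make the invitations; Blinding says they know the arms. The manager's own masking is not described, but whoever makes the assignment necessarily knows it.

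3. **Can the companies be told apart beforehand?** Yes. According to Setting and the company criteria, they are large clients of one insurer in three cities, and their support for the study and for a wait-list place is discussed at recruitment. The Randomisation section has the manager number the companies themselves and mentions no coded list.

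4. **How much room does the procedure leave?** Less than it may seem. A random numbers table is a sound source, and the numbers are assigned before it is used. If the starting point and reading rule are fixed in advance, the order of numbering cannot influence the result unless the table entries are already known. What remains is the choice of starting point and the possibility of a repeat draw. With one person doing both steps, the procedure as described would not bring either to light.

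5. **Does commitment come before allocation?** Probably. Randomisation speaks of companies that are already participating, and the company criteria ask prospective companies for the letter of commitment. Neither section says that all companies are then allocated in one joint draw rather than as they join.

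6. **Could the analysis repair an imbalance?** In part. Table 3 places a baseline measurement before counselling, the HRA questionnaire section records readiness to change physical activity, and the primary outcome is itself a change. Adjustment for these would take up some difference in motivation. Management support is a company-level trait and is not among the measures the article lists, so full repair cannot be assumed.

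**The case against.** The strongest reply is that the article describes a valid random source used in a safe order, and that the starting point, the reading rule and the timing of the draw are details an article commonly leaves to the full protocol. That is right: their absence is no finding. What stands is the stated choice of allocator, which would remain a poor one even if those details were fixed elsewhere.

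Some stronger readings are tempting, and the documents do not support them:

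- **That the manager has an interest in the result, or a workload that depends on it.** This would be an inference from the job title. No conflict is declared, and neither the manager's employer nor workload is described.
- **That the draw was or will be steered.** Nothing in the text indicates it.
- **That companies may be allocated before they commit.** The wording of the two relevant sections points the other way.
- **That any resulting bias is beyond adjustment.** Baseline activity and readiness to change are both recorded.
- **That one misplaced company would distort an arm by a known percentage.** That needs a number of companies that the article does not give, and a share of an arm is not an estimate of bias in the outcome.

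Two practical objections also have weight. Unblinded specialists invite individual employees, and the article does not place enrolment before allocation. That is a more direct route to selection, and changing the allocator does not close it. In addition, the Blinding section says in the past tense that the specialists "knew which companies were receiving the intervention", so some allocation may already have taken place.

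**Conclusion.** The point holds as one about independence. Allocation of the randomised unit is given to the manager of the staff who recruit and treat, and the stated procedure has no independent check. This rests on the text of the Randomisation section read with Step 4, Study population, Intervention group and Blinding, and on no assumed figure.

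No size can be attached to it. The consequence is a weaker safeguard and a draw that would be hard to defend if questioned; a demonstrated bias is not shown. It does not make the trial invalid. It is worth acting on because the remedy is specific and cheap.

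**What to change.** Amend the Randomisation section to say that:

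- a member of the research team who is not involved in recruitment or counselling makes the allocation;
- all companies with a signed letter of commitment are allocated in one draw;
- the draw uses a list of codes without company names;
- the computer seed, or the starting point and reading rule of the table, is recorded;
- the wellness specialists' manager is told the result only afterwards.

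The cost is a short rewrite and a little time from existing research staff. The intervention, outcomes and sample size do not change. The downside is a possible short delay while the last commitment letters come in.

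If the draw has already been made, report who made it, when, for which companies, and whether the starting point was fixed and the draw made once.

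The same paragraph names two groups, whereas Study design and Intervention group describe two counselling schedules plus control. That is a separate matter, but the amended text should also say how companies are assigned between the two schedules.
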